#### 2.6.3. Other Outcomes

-Cognition

Changes in the Montreal Cognitive Assessment (MoCA), which is a cognitive screening test designed to detection cognitive impairment will be recorded. The MoCA has a good predictive value for the development of poststroke cognitive impairment in the follow-up when used in the acute stage after stroke [37]. It assesses different cognitive domains: attention and concentration, executive functions, memory, language, visuo-constructional skills, conceptual thinking, calculations, and orientation.

-Dependency in daily living activities

The Modified Rankin Scale is used for measuring the degree of disability or dependence in the daily activities of patients after stroke. It is the most widely used clinical outcome measure after stroke. The scale has six points, and a higher score indicates a worse outcome. The minimum score is 0 points, indicating no symptoms at all, and the maximum score is 6 points, indicating death [38]. The Barthel index is a scale used to measure performance in activities of daily living (ADL). The maximum score is 100 points. The BI has excellent inter-rater reliability as a stroke outcome measure [38].

-Clinical assessment of gait-related task

The Timed Up and Go (TUG) test is a clinical test that is used to assess a person’s mobility, which requires both static and dynamic balance. The objective of this test is to determine fall risk and measure the progress of balance, sit to stand, and walking. There is no defined value of the minimal clinically important difference for stroke patients; however, [39] showed that a change of ≥28% can indicate a relevant difference.

-Lower limb muscle strength

Lower limb muscle strength testing, where a grading of 0–5 reflects the maximum force executed by a certain muscle [40,41], will be conducted. Lower limb muscle strength is associated with gait recovery, and a grade ≥3 represents a predictor of independent walking after stroke [40].

-Lower limb muscle activity during walking

Changes in lower limb muscle activity (medial gastrocnemius, tibialis anterior, quadriceps, and hamstrings) during treadmill gait and overground walking will be measured by bipolar surface electromyography (Delsys Trigno Avanti wireless EMG/IMU sensor system, Delsys, Natick, MA, United States) according to International Society of Electrophysiology and Kinesiology [42]. Inertial measurement units (IMUs) have been validated to measure movement quality in clinical settings [43]. EMG/IMU sensors with built-in triaxial accelerometers and triaxial gyroscopes will also be used to identify the course of the stance and the swing phase during treadmill and overground walking for both the paretic and nonparetic limbs [44]. The changes in the lower limb muscular activation patterns resulting from robotic or conventional gait training may help to identify the physiological gait characteristics in patients after stroke [43,45].

-Depression

Changes in score on the Beck Depression Inventory Scale—a 21-item self-report rating inventory that measures characteristic attitudes and symptoms of depression—will be recorded. Each item (question) has a set of at least four possible responses that range in intensity. Scores of 0–9 indicate minimal depression, and scores of 30–63 points indicate severe depression. Higher total scores indicate more severe depressive symptoms.

-Quality of Life

Changes in the score on the EQ-5D-3L Questionnaire’s standard layout for recording an adult person’s current self-reported health state will be recorded. This questionnaire consists of a standard format for respondents to record their health state according to the EQ-5D-3L descriptive system and the EQ VAS.

### 2.7. Sample Size

Based on an analysis of our pilot data concerning the gait velocity (primary outcome), 120 participants (60 in each group) are anticipated to be enrolled in this study. This number of participants would provide 85% power (α level 5%) to detect a difference of 0.16 m/s in the 10 MWT (with respect to a missing data rate of 15% and an expected 10% drop in the follow-ups) between groups after intensive rehabilitation with add-on intervention. The gait speed difference of over 0.16 m/s was previously defined as the minimal clinically important difference in gait speed in subacute stroke patients [46].

For the multimodal magnetic resonance imaging (MRI), including functional MRI (fMRI), we have estimated that a sample size of 50 participants (25 in each group) will suffice to find significant correlations of MRI outcomes with gait recovery. This is based on previous studies of fMRI and gait recovery in similar clinical cohorts [29,32]. We will perform multimodal MRI in half of the randomly selected enrolled IS patients (1:2 randomization), i.e., in 60 participants, to allow for a common drop-out of examined patients with MR images of poor or insufficient quality. As we do not have sufficient information to estimate the variance in the outcomes, we plan to calculate the definitive effect sizes based on the interim analysis of the first 30 subjects measured within all four visits (visit 1–visit 4).

### 2.8. Randomization

The randomization of the enrolled participants for robot-assisted treadmill gait training (RTGT) or therapist-assisted treadmill gait training (TTGT) will be performed as a block randomization with a 1:1 allocation to either RRGT or TTGT. As mentioned above, in randomly selected IS patients with a 1:2 allocation, a repeated multimodal magnetic resonance imaging (MRI) examination, including functional MRI (fMRI), will be performed during the study follow-up.

Participants will be randomized after the screening of eligible participants by the certificated neurologist at the Comprehensive Stroke Centre and before the first clinical visit (visit 1).

Participants will be randomized in a 1:1 ratio and in a 1:2 ratio to multimodal magnetic resonance imaging (MRI) using the web randomization module. A randomized web number generator will be implemented for group allocation. Neurologists will generate the allocation sequences, enroll the participants, and assign the participants to interventions.

The allocation might be adaptively modified in cases when patients randomized for RTGT, after enrolment and during the course of rehabilitation, will be identified as independent walkers (FAC > 3). This change will be reported. It has previously been identified that stroke survivors with gait deficits (FAC ≤ 3) with higher motor impairment are those who benefit the most from robot-assisted therapy in combination with conventional therapy [15,23,47,48].

All participating patients will obtain a card before discharge (visit 2) with the dates of all scheduled outpatient events (visit 3 and visit 4), including the dates of the fMRI examinations and even the telephone contacts with the study investigators (neurologist and principal physiotherapist). All enrolled patients will be promoted and motivated to remain in the study and complete follow-ups during each scheduled visit. In participants who discontinue or deviate from the intervention protocols, the acquired outcome data will be collected for a further subanalysis.

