## Abstract

The GAITFAST study (gait recovery in patients after acute ischemic stroke) aims to compare the effects of treadmill-based robot-assisted gait training (RTGT) and therapist-assisted treadmill gait training (TTGT) added to conventional physical therapy in first-ever ischemic stroke patients. GAITFAST (Clinicaltrials.gov identifier: NCT04824482) was designed as a single-blind single-center prospective randomized clinical trial with two parallel groups and a primary endpoint of gait speed recovery up to 6 months after ischemic stroke. A total of 120 eligible and enrolled participants will be randomly allocated (1:1) in TTGT or RTGT. All enrolled patients will undergo a 2-week intensive inpatient rehabilitation including TTGT or RTGT followed by four clinical assessments (at the beginning of inpatient rehabilitation 8–15 days after stroke onset, after 2 weeks, and 3 and 6 months after the first assessment). Every clinical assessment will include the assessment of gait speed and walking dependency, fMRI activation measures, neurological and sensorimotor impairments, and gait biomechanics. In a random selection (1:2) of the 120 enrolled patients, multimodal magnetic resonance imaging (MRI) data will be acquired and analyzed. This study will provide insight into the mechanisms behind poststroke gait behavioral changes resulting from intensive rehabilitation including assisted gait training (RTGT or TTGT) in early subacute IS patients.

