### 2.3. Interventional Methods

#### Interventions

Enrolled participants will be randomly allocated into two groups before the start of the intensive rehabilitation at the Department of Rehabilitation at the University Hospital Olomouc, Czech Republic

Robot-assisted treadmill gait training (RTGT) is locomotor training guided by a robotic device Lokomat (Hocoma, Volketswil, Switzerland) on a treadmill according to a preprogrammed gait pattern with a robot-driven exoskeleton orthosis. The process of gait training is automated and controlled by a computer. The parameters of RTGT, such as guidance force or gait speed, are adaptively adjusted with respect to the patient’s actual walking abilities by a trained physiotherapist with at least 2 years of clinical experience on the Lokomat. Moreover, the dynamic body weight support system within this type of therapy is adjustable to the actual patient’s body-weight-bearing tolerance. RTGT is always realized under the supervision of a physiotherapist.

Therapist-assisted treadmill gait training (TTGT) is locomotor training via the repetitive execution of walking movements that are manually guided by a physiotherapist during treadmill gait training. Body weight support might be provided to patients during this type of gait training, if needed. Body weight support and gait speed are also adaptively adjusted with respect to the patient’s actual walking abilities as is the assistance, which is manually provided by physiotherapists with at least 4 years of clinical neurorehabilitation practice with poststroke patients. TTGT still represents a comparable type of training to RTGT, where each step might be adaptively corrected by the physiotherapist. However, the symmetrical stereotypical gait pattern might only be achieved in RTGT.

Assisted gait training (RTGT or TTGT) is performed five times per week, with durations of up to 30 min [23] for two weeks as an add-on therapy to conventional physical therapy. Adherence to the therapy is ensured by the adjustment of RTGT or TTGT according to the patient’s comfortable speed, actual need of body weight support, and his or her training intensity tolerance.

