### 2.4. Blinding Procedure

All enrolled participants will be assessed by investigators that will be blinded to the group allocation. The physiotherapists performing the interventions (RTGT or TTGT) will not be blinded; however, they will not participate in the assessments at all and will not have any access to the interim and final results and outcomes. Although it is impossible to blind the participants due to the interventional study design, the participants will be instructed not to disclose their allocation to the investigators or the outcome assessors.

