### 2.5. Study Protocol

All enrolled participants will be examined by evaluators that will be blinded to the group allocation. The assessments will be realized by certified neurologists, rehabilitation physicians, physiotherapists, and biomedical engineers with respect to their specialization at four assessment timepoints. Clinical visits will occur as follows:

Visit 0 (T0): enrolment 5–10 days after onset of qualifying IS at the Comprehensive Stroke Centre.

Visit 1 (T1) (3–5 days after V0): assessment before the initiation of an intensive rehabilitation program including assisted gait training (RTGT or TTGT) at the Department of Rehabilitation.

Visit 2 (T2) (14 ± 7 days after visit 1 and 1 month after visit 0): assessment at the end of the intensive rehabilitation program including gait training at the Department of Rehabilitation.

Visit 3 (T3): assessment 12 ± 1 weeks after visit 0 (3 months after visit 0).

Visit 4 (T4): assessment 24 ± 2 weeks after visit 0 (6 months after visit 0).

Scheduled outpatient visits in the GAITFAST trial will be performed by a neurologist at the Department of Neurology (visit 1–visit 4), a rehabilitation physician, a physiotherapist, and a biomedical engineer at the Kinesiology Laboratory at the Department of Rehabilitation (visit 1–visit 4). Multimodal MRI data will be acquired on a 3T scanner (Siemens Magnetom Vida, Erlangen, Germany) at the Department of Radiology. Scanning will be supervised by a member of the Functional Magnetic Resonance Imaging Laboratory (visit 1–visit 4). The duration of patient participation will be 6 months (Table 1).

Each visit will include an assessment to evaluate gait speed, gait dependency, neurological impairment, sensorimotor function, and gait biomechanics and a multimodal MRI of the brain. The outcome variables and study flow are presented in more detail in Table 2.

As data accumulate, the validity and the integrity of the trial will be subjected to an interim analysis after the first 30 participants have been assessed at all four assessment timepoints. With respect to the results of the interim analysis, the study design (such as the sample size, allocation ratio, or eligibility criteria) might be adaptively modified.

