#### 2.6.1. Primary Outcome

Walking speed is defined as a primary outcome in this study and is the most used outcome measure of walking ability in locomotor rehabilitation. Walking speed has been shown to be a predictor of independence, the functional level at home and within the community, and quality of life [25]. Gait speed will be evaluated before the beginning of inpatient RHB, after two weeks (at the end of inpatient RHB), and during follow-up (three and six months after stroke onset). Gait speed will be measured using the 10-meter walking test. The subject will be asked to walk a distance of 10 m at his/her comfortable speed. The time will be measured for the distance of the middle six meters, which will reflect walking acceleration and deceleration. If the physical assistance of another person (to prevent a fall or collapsing) is needed for a patient to complete the test, the level of assistance will be documented. If total assistance or assistance for limb swing or forward propulsion is required, a walking speed of 0 m/s will be documented [26]. The usage of any assistive device and/or bracing (that patients use for walking and are needed to complete the test) will also be documented. Based on the gait speed, walking may be classified as household (<0.4 m.s^−1^), limited community (0.4 to 0.8 m.s^−1^), or full community ambulation (>0.8 m.s^−1^) [20].

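### Treatment is allocated at Visit 0, but gait speed is first measured 3–5 days later at Visit 1, so the primary baseline is a post-randomisation value in unblinded patients who may already know their arm

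*Protocol article*

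**What the plan says.** All references are to the protocol article.

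- **Allocation.** Section 2.8 has patients randomised after screening, "at the Comprehensive Stroke Centre and before the first clinical visit (visit 1"; Table 1 has its single allocation mark at Visit 0 and labels Visit 1 as post-allocation. Section 2.3 asks for less: participants "will be randomly allocated into two groups before the start of the intensive rehabilitation".
- **Visit dates.** Section 2.5 gives "Visit 0 (T0): enrolment 5–10 days after onset of qualifying IS at the Comprehensive Stroke Centre" and then "Visit 1 (T1) (3–5 days after V0): assessment before the initiation of an intensive rehabilitation program".
- **First outcome measurement.** Section 2.6.1: "Gait speed will be evaluated before the beginning of inpatient RHB, after two weeks (at the end of inpatient RHB), and during follow-up". Table 2 marks the 10-metre walk test, FMA-LE and treadmill gait analysis from T1, with no T0 entry. Section 2.5 schedules the multimodal MRI for visits 1 to 4.
- **Measured at enrolment.** The eligibility criteria in section 2.2.1 use FAC and NIHSS at enrolment, and Table 2 also marks NIHSS at T0.
- **Blinding.** Section 2.4 says "it is impossible to blind the participants due to the interventional study design". Assessors are blinded, and patients are told not to reveal their arm to them.
- **Use of T1.** Section 2.10 analyses groups and time points over visits 1–4 by mixed ANOVA if the data are normal. If they are not, it uses Friedman tests within group and Mann–Whitney tests between groups. Section 2.6.2 compares the post-training minus pre-training fMRI difference between groups.

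**The concern.** A baseline has two uses in a randomised comparison: it describes the groups before treatment can have influenced them, and it is the reference for change. Both uses assume that the value cannot depend on the arm. Here no gait-speed value exists from before allocation.

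The patients are unblinded and the test is walked at a speed the patient chooses. Blinded assessors protect the timing and scoring of the walk, but not the patient's own behaviour. If knowing the arm altered effort or confidence at T1, the alteration would sit in the reference value.

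The second consequence does not depend on what patients know. Anyone who withdraws, is discharged or is excluded between T0 and T1 is already randomised but has no gait speed at any visit. Section 2.5 excludes patients with a recurrent stroke or a new condition affecting mobility; if that happens in the gap, it is a loss after randomisation with no outcome and no primary baseline.

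**Working it through.** **1. The gap.** Inputs: T0 at day 5–10 after onset and T1 at 3–5 days after T0 (section 2.5).

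- Earliest T1: 5 + 3 = day 8.
- Latest T1: 10 + 5 = day 15.

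This reproduces the abstract's own figure for the first assessment, "at the beginning of inpatient rehabilitation 8–15 days after stroke onset". Three places (section 2.5, Table 1, abstract) therefore agree, and with allocation at T0 the interval from allocation to baseline is 3–5 days.

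**2. Which baselines are affected.**

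| Measure | Value before allocation? | First scheduled outcome assessment |
|---|---|---|
| Gait speed (primary) | No | T1 |
| FMA-LE | No | T1 |
| Gait biomechanics | No | T1 |
| Study multimodal MRI | No | T1 |
| FAC | Yes, eligibility score | T1 |
| NIHSS | Yes, eligibility score and T0 mark | T0 |

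**3. How a shift at T1 would enter the analysis.** Let b1 be the between-arm difference at T1 caused by knowledge of the arm, and b2 the corresponding difference at a later visit.

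- Change from T1 to the later visit: bias = b2 − b1.
- If the shift is the same at both visits (b1 = b2), it cancels: bias = 0.
- If it is present at T1 and gone later (b2 = 0): bias = −b1, that is, one for one.
- Comparison of later values alone: bias = b2; T1 does not enter.

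The group-by-time term of the mixed ANOVA and the pre/post fMRI difference are contrasts of the first kind. A Mann–Whitney test on post-treatment values would be of the last kind; section 2.10 does not say whether change scores or visit values are compared.

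**4. Scale.** The documents give no figure for b1. As an assumption only, for a shift confined to T1, relative to the 0.16 m/s in section 2.7:

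- b1 = 0: no bias.
- b1 = 0.02 m/s: 0.02 / 0.16 = 12.5%.
- b1 = 0.05 m/s: 0.05 / 0.16 = 31%.

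These figures convert an assumed shift into a share of the target difference; they are not estimates.

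**5. Whether the early timing is required.** Section 2.3 needs allocation before intensive rehabilitation starts. Section 2.5 puts T1 before that start as well. Allocation after T1 and before the first session satisfies both sections.

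**The case against.** The case against has several sound parts.

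- **Knowledge of the arm is inferred.** A reader might conclude that patients know their arm at T1. The article never says when they are told. The instruction not to disclose it makes early knowledge plausible, and nothing withholds it until T1, but the documents support only that patients may know.
- **Not every baseline is affected.** FAC and NIHSS are scored at enrolment, so a statement covering all baselines would be wrong.
- **The bias needs a particular pattern.** Patients remain unblinded at T2–T4, and an equal shift at all visits cancels in the change contrast. Both arms receive active assisted treadmill training on top of the same conventional programme, so even the direction is unclear. This stands. The cancellation is not something the plan can rely on, however, because it requires the effect of knowing the arm to be the same before training as after it.
- **The powered comparison may not use T1.** Section 2.7 powers a difference between groups after intensive rehabilitation, and no baseline adjustment of gait speed is planned; the only ANCOVA in section 2.10 is for fMRI. It would therefore be unsupported to say that a T1 shift must pass into the treatment effect. It applies to the mixed ANOVA and to change contrasts.
- **Losses in the gap may be few.** The interval is short and both departments are in the same hospital. Section 2.7 also allows for 15% missing data and a 10% drop in follow-up. That allowance protects power; it does not restore comparability if losses differ by arm.
- **Early allocation may have a practical reason.** The Stroke Centre neurologists randomise and another department treats, so advance booking is a plausible motive, although the article does not state one.

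It is also tempting to tie this to the rule that "The allocation might be adaptively modified in cases when patients randomized for RTGT" become independent walkers. That rule also applies during rehabilitation, and eligibility is fixed at enrolment. Later allocation would therefore not remove it, and it is a separate issue.

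**Conclusion.** The point holds as a weakness in the order of events. The sequence is explicit and consistent across the document: allocation at T0, and first gait speed, FMA-LE, biomechanics and study MRI 3–5 days later, in patients who are not blinded.

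Two consequences follow. First, the change contrasts are open to bias from any arm-related shift at T1 that does not persist equally at later visits. This rests on patients learning their arm before T1 and on that knowledge affecting performance; its size and direction are unknown and it may be zero. A comparison of post-treatment values alone is not exposed to it. Second, patients lost between T0 and T1 count as randomised but have no gait-speed value. This needs no assumption about behaviour, but the number of such patients cannot be derived from the document.

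This does not show that the trial's result will be biased. It is a cheap improvement, worth making because the present order has no stated benefit and the affected baseline is that of the primary outcome.

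**What to change.** Amend section 2.8 and Table 1 so that the web module releases the treatment allocation only after the T1 assessments are completed and locked, and before the first training session. In Table 1, move the allocation mark from Visit 0 to after Visit 1, and correct the post-allocation label over Visit 1. Section 2.3 needs no change.

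The separate draw for the MRI subset can stay at T0 so that the T1 scan can be booked. If patients have already been randomised under the present order, record the date of the change so that the two periods can be told apart.

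The cost is a short amendment, one altered step in the web module, and less notice for booking robot or treadmill slots. The change does not address arm-related behaviour at T2–T4 or the RTGT-only reallocation rule; the latter has to be dealt with separately.

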#### 2.2.2. Screening and Recruitment

The screening of eligible participants with acute IS and their randomization for the GAITFAST trial will be performed by a certified neurologist at the Comprehensive Stroke Centre (University Hospital Olomouc). The neurologist will provide an overview of the study and determine initial interest in participation. All the potential risks and benefits related to study participation will be discussed with the participants. Potential participants will be informed that participating in the study is completely voluntary and that they may discontinue participation at any time. For individuals who express interest, the neurologist will determine initial eligibility and answer any participant questions. For individuals who agree to participate in this study and provide consent, the neurologist will perform screening procedures to confirm that the patient meets the eligibility criteria. By signing the informed consent, the participants will provide permission for the study investigators to obtain, collect, and analyze relevant data and to share them anonymously with the other members of the research team as well as to present or publish them anonymously at scientific conferences or in scientific journals. Regular screening of the study eligibility of all admitted patients with IS at the Comprehensive Stroke Centre by neurologists and physiotherapists (study investigators) will be performed every 2–3 days. Enough time will be given for the discussion with each eligible patient on his/her participation in the study, the study flow-chart, the importance of study follow-up, and informed consent.

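### Neurologists who enrol also generate the block sequence and assign treatment, so concealment is not secured, and no rule separates them from the blinded neurologist assessors

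*Protocol article*

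**What the plan says.** On allocation, section 2.8 of the protocol article states that randomization "will be performed as a block randomization with a 1:1 allocation", carried out "using the web randomization module. A randomized web number generator will be implemented for group allocation". The sentence that follows gives three tasks to one role: "Neurologists will generate the allocation sequences, enroll the participants, and assign the participants to interventions". Section 2.2.2 agrees: "The screening of eligible participants with acute IS and their randomization for the GAITFAST trial will be performed by a certified neurologist". The same section has the neurologist present the study, obtain interest and consent, and confirm eligibility. Randomization follows screening and precedes visit 1. Block size, the holder of the list and the moment of release are not given.

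On assessment, section 2.4 states: "All enrolled participants will be assessed by investigators that will be blinded to the group allocation". It then excludes the treating physiotherapists from assessment and from access to results. Section 2.5 repeats that evaluators are blinded, and adds: "The assessments will be realized by certified neurologists, rehabilitation physicians, physiotherapists, and biomedical engineers". It also says: "Scheduled outpatient visits in the GAITFAST trial will be performed by a neurologist at the Department of Neurology", covering visits 1 to 4. No sentence says whether these neurologists are the ones who randomize.

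**The concern.** Concealment requires that the person deciding whether to enrol a patient cannot know the next assignment. Read literally, section 2.8 gives the sequence to exactly that person.

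The setting adds to the exposure. The trial has one centre (section 2.1), and neither participants nor treating therapists can be blinded (section 2.4), so past assignments are easy to learn. Several entry criteria in section 2.2.1 need judgement, for example whether another condition limits walking. Recruiters may also hold a view on who gains from the robot: section 2.8 cites evidence that more impaired dependent walkers benefit most.

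At stake is the comparability of the arms. Selective enrolment by prognosis would affect every outcome, including the primary one. Adjustment for measured baseline factors would not remove selection on unmeasured ones.

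The second issue is assessor blinding. Whoever assigned a patient knows the arm. If that person later scores the same patient, the blinding statement fails for those scores. The plan recognises this risk for the physiotherapists but sets no matching rule for the neurologists.

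**Working it through.** The plan gives no figure on this point to reproduce. The check is a comparison of the text, followed by an illustration of predictability.

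**Who does what**

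| Task | Role named | Section |
|---|---|---|
| Screening, consent discussion, eligibility | Certified neurologist, Comprehensive Stroke Centre | 2.2.2 |
| Generating the sequence | Neurologists | 2.8 |
| Enrolling and assigning | Neurologists | 2.8 |
| Tool | Web module and number generator; custody of the list not stated | 2.8 |
| Visits 1 to 4 | A neurologist at the Department of Neurology, with other specialists at the Kinesiology Laboratory | 2.5 |
| Barred from assessing | Treating physiotherapists only | 2.4 |

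1. One role covers generation, enrolment and assignment. No independent list holder and no release step is described.
2. Neurologists stand on both sides of the blinding line, as assigners in 2.8 and as assessors in 2.5. The only separation rule concerns a different profession.
3. The locations differ in name (Comprehensive Stroke Centre and Department of Neurology) and no individuals are identified. The text therefore neither shows nor excludes that the same people do both.
4. Table 2 schedules the NIHSS, a secondary outcome, at T1 to T4. No section says who scores it at those visits or who times the 10-metre walk.

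**How much could be foreseen**

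A person holding the generated list knows 100% of assignments.

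A person without the list, who knows a fixed block size and all earlier assignments, is certain of an assignment once one arm of the block is used up. In a block of size 2m, the m places of one arm split the m places of the other into m + 1 gaps of equal expected size. The expected run left at the end of the block is therefore 2 × m/(m + 1), and the certain share is [2m/(m + 1)]/(2m) = 1/(m + 1).

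Direct count for blocks of 4: of the 6 arrangements, 2 leave two certain positions and 4 leave one, so (2 × 2 + 4 × 1)/(6 × 4) = 8/24 = 33%.

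| Assumed fixed block | m | Certain share 1/(m + 1) | Of 120 patients |
|---|---|---|---|
| 2 | 1 | 50% | 60 |
| 4 | 2 | 33% | 40 |
| 6 | 3 | 25% | 30 |
| 8 | 4 | 20% | 24 |

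The article states no block size, so these are assumptions shown as a range.

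**The case against.** The strongest reply is the web module. If it generates the list and shows one assignment at a time after registration, then generating the sequence may mean no more than operating the module, and concealment would hold. The order of consent, eligibility check and randomization fits that reading. The article also mentions a full protocol that is not shown, and custody of the list and block size are details that an article often leaves there.

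Much of this stands. A reader might infer that concealment is removed; the documents do not support that, because a locked module could preserve it. The reply does not clear the point, however. The article does not merely omit who generates the sequence: it names the recruiters. If the module does the work, that sentence is wrong and still needs correcting.

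A reader might also infer that the recruiting neurologists examine their own patients at visits 1 to 4, which would contradict the blinding statement outright. That rests only on a shared job title, and the reply stands on this.

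Nor is assessor bias shown for the primary outcome. Section 2.5 divides assessments by specialization, and the 10-metre walk is not assigned to a neurologist.

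The suggested motive is also limited. All eligible patients are already in FAC 1 to 3, so only the remark about higher motor impairment could steer selection within the trial population.

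**Conclusion.** The point holds as a defect in a stated procedure. As written in sections 2.2.2 and 2.8, allocation concealment is not secured. This part of the point reaches the primary outcome, because selection at entry affects everything measured afterwards.

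On blinding, the finding is an overlap of roles with no separating rule. Sections 2.4, 2.5 and 2.8 need to be reconciled, but a contradiction is not proven.

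The size depends on facts not given. Foreseeability is 100% if recruiters can see the list, and 20% to 50% for assumed fixed blocks of 8 down to 2 if they know the block size and past assignments. With a module that holds the list under undisclosed, varying block sizes, these certain predictions would largely disappear. The resulting bias in gait speed cannot be quantified from the document.

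**What to change.** Replace the sentence in section 2.8 so that it states:

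- the web module already planned generates and holds the sequence, and nobody who recruits can see it;
- block sizes are undisclosed and preferably vary;
- the neurologist registers the eligible, consented patient irrevocably, and only then is the assignment released;
- the assignment goes to the treating physiotherapists, who are unblinded in any case.

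Add to section 2.4 that any neurologist who knows a patient's allocation does not score that patient's outcomes at T1 to T4. Bring section 2.2.2 into line, so that the neurologist registers patients and does not generate or see the list.

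The cost is configuration of the module, a change in who receives the randomization notice, and edited wording. Where a neurologist does learn an allocation, for example from the patient, a second neurologist must be available for that patient's neurologist-rated scores. Routing the notice to the physiotherapists should keep such cases few.
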